### Clinical variables recorded to check the degree of suitability of the guideline recommendations

Previous episodes and treatment, diagnosis and current therapeutic plan, and reason for referral to mental health.

### Sociodemographic variables recorded

Age, gender, nationality, time of residence in Spain, and employment status.

### Variables recorded for family physicians (cluster level)

Age, gender, years of professional activity, training in interview skills, training in psychological intervention techniques, average number of patients attended in three months, and evaluation about usefulness of the guide and modification of its clinical practice.

### Data collection method

#### Professionals

Data will be collected by telephone interview by a member of the research team before randomisation. All data will be collected except the number of patients visited, which will be taken from the health information system. Opinion will be collected at the end of the study.

### Patients

The clinical interview will be used and the data will be recorded in an electronic data collection log especially designed for this study. The different variables will be collected over four follow-up visits: baseline, three, six, and twelve months. The Figure 1 shows the flowchart of the study.

**Figure 1 F1:**
[figure not shown]
**Flowchart**.

### Statistical analysis

This will be based on the principle of intention to treat. The use of the design by clusters chosen will be taken into account in all phases of data analysis, especially in the calculation of the confidence intervals (CI) of the estimates and in the hypothesis tests:

1. Descriptive analysis of each variable with its corresponding CI at 95%. Tests for normality. Description of losses and quitting.

2. Comparison of the group at the beginning of the trial with regards to response variables, descriptive variables, and prediction factors. Bivariate statistical tests will be used suitable to the type of variable (qualitative or quantitative).

3. Analysis of primary outcome. There will be a comparison of the percentage of patients with a reduction of two or more points on the Goldberg anxiety subscale at six and twelve months from the intervention in both groups by the chi-squared test, and the confidence interval of the difference will be calculated. Confounding variables will be controlled with multivariate analysis based on logistic regression with random effects.

4. Analysis of secondary outcome. For each of the secondary response variables the results of the variables will be compared based on the group assigned by calculating the difference in proportions of each variable.

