**Method/design:**

This study involves a community based on cluster randomized trial in primary healthcare centres in the Madrid Region (Spain). The project aims to determine whether the use of implementation strategy (including training session, information, opinion leader, reminders, audit, and feed-back) of CPG for patients with anxiety disorders in primary care is more effective than usual diffusion.

The number of patients required is 296 (148 in each arm), all older than 18 years and diagnosed with generalized anxiety disorder, panic disorder, and panic attacks by the Diagnostic and Statistical Manual of Mental Disorders-IV (DSM-IV). They are chosen by consecutive sampling.

The main outcome variable is the change in two or more points into Goldberg anxiety scale at six and twelve months. Secondary outcome variables include quality of life (EuroQol 5D), and degree of compliance with the CPG recommendations on treatment, information, and referrals to mental health services. Main effectiveness will be analyzed by comparing the patients percentage improvement on the Goldberg scale between the intervention group and the control group. Logistic regression with random effects will be used to adjust for prognostic factors. Confounding factors or factors that might alter the effect recorded will be taken into account in this analysis.

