## Methods/design

### Design of the study

This study is a two-year community, parallel clinical trial, randomised by clusters, that compares two different CPG implementation strategies. The intervention will be made on health professionals (physicians, nurses, and social workers) of primary healthcare centres (PHCC) in the region of Madrid, Spain. The randomization units will be PHCCs (clusters). The units of analysis are patients of health professionals (individual level) of the PHCCs participating in the study (as a control or intervention) according to the CONSORT checklist (additional file 1).

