### Sample size

#### Method of calculation

For an alpha of 0,05, a power of 80% and in order to detect a decrease in the Goldberg Scale (two or more points) of 20% in the intervention group, the overall simple size required 206 patients (103 in each arm of the study). Because randomisation was by cluster, the sample size had to be larger than if simple randomisation had been performed, in order to take into account the design effect (DE). The DE was calculated as follows: DE = 1 + (n_c _- 1) * ICC (where n_c _is the mean number of individuals in the cluster, and ICC the intracluster correlation coefficient) [36]. The ICC in the present work was deemed to be 0.01. The mean cluster size was assumed to be 20 patients. Given these assumptions, and expecting a 20% loss rate, the final sample size required was 296 patients (148 in each arm).

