### Sequence generation

The 16 PHCCs will be assigned to the intervention or the control group following a simple, computer-generated random sequence (EPIDAT 3.1).

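### The plan promises that tests and confidence intervals will allow for clustering, but the test it names for the primary outcome is a chi-squared test, which does not, and neither of its two analyses is made decisive

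*Protocol article*

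**What the plan says.** All references are to the protocol article.

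- **Sequence generation** fixes the unit of randomisation: "The 16 PHCCs will be assigned to the intervention or the control group following a simple, computer-generated random sequence". **Design of the study** says that the analysis is at patient level: "The units of analysis are patients of health professionals (individual level) of the PHCCs participating in the study".
- **Sample size** inflates the number of patients by a design effect, with a mean cluster size of 20. On the correlation it says: "The ICC in the present work was deemed to be 0.01".
- **Statistical analysis, opening paragraph**, makes a general commitment: "The use of the design by clusters chosen will be taken into account in all phases of data analysis". It singles out confidence intervals and hypothesis tests, and it introduces items 1 to 4.
- **Statistical analysis, item 3**, compares the percentages of patients who improve by two or more points on the Goldberg anxiety subscale "in both groups by the chi-squared test, and the confidence interval of the difference will be calculated". A separate sentence then assigns random-effects logistic regression to the control of confounding variables.
- **Abstract, Method/design**, follows the same order. Main effectiveness is a comparison of percentages, and then: "Logistic regression with random effects will be used to adjust for prognostic factors".

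**The concern.** The sample size section accepts that patients of one centre resemble each other. The test named for the primary outcome assumes, in its usual form, that they do not. The only named method that can carry a centre effect is the random-effects model, and both item 3 and the abstract give it a different job, which is covariate adjustment.

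Two things are at stake. First, an analyst who follows item 3 to the letter would report a p-value that is too small and an interval that is too narrow. An analyst who follows the opening paragraph has no named method to use. Second, item 3 gives two analyses of one outcome without ranking them. If they disagree, either could be presented as the primary result.

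**Working it through.** **1. The plan's own figure.** Inputs from the sample size section: 103 patients per arm before inflation, intracluster correlation (ICC) 0.01, mean cluster size 20, loss 20%.

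- Design effect: DE = 1 + (20 − 1) × 0.01 = 1.19.
- Per arm: 103 × 1.19 = 122.6, rounded up to 123. Then 123 × 1.2 = 147.6, rounded up to 148.
- Total: 2 × 148 = 296, as stated. The plan therefore does rely on a design effect of 1.19.

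**2. Patients per centre at analysis.** 296 / 16 = 18.5 recruited per centre. After 20% loss, 0.8 × 18.5 = 14.8. I use 14.8 as the lower value and the plan's 20 as the upper.

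**3. Effect of ignoring clustering.** A test that treats patients as independent understates the standard error by a factor √DE. So:

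- true two-sided type I error = 2 × [1 − Φ(1.96 / √DE)]
- shortfall in interval width = 1 − 1/√DE

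The article does not state whether alpha is one- or two-sided. Two-sided is assumed.

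| ICC | Patients per centre | DE | √DE | Type I error | Interval too narrow by |
|---|---|---|---|---|---|
| 0.01 (plan) | 14.8 | 1.138 | 1.067 | 6.6% | 6% |
| 0.01 (plan) | 20 | 1.19 | 1.091 | 7.2% | 8% |
| 0.05 (assumed) | 14.8 | 1.69 | 1.300 | 13.2% | 23% |
| 0.05 (assumed) | 20 | 1.95 | 1.396 | 16.0% | 28% |

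At the plan's ICC, the nominal 95% interval would cover 93.4% to 92.8% of the time.

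**4. Check by simulation.** Beta-binomial data, 8 centres per arm (assumed, since simple randomisation does not guarantee an even split), 15 to 20 patients per centre, and response rates assumed between 30% and 50%:

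- Uncorrected chi-squared test, ICC 0.01: mostly 6.5 to 7.3% rejections under the null. Because the table is discrete, single settings fall outside this range (5.9% in one run with 15 per centre, 7.4% in one with 18).
- Uncorrected chi-squared test, ICC 0.05: about 13 to 16%.
- Chi-squared statistic divided by the true design effect, ICC 0.01 to 0.05: 4.6 to 5.7%.
- t-test on centre proportions: 4.8 to 5.2%.

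**5. What a centre-level test costs.** With 16 contributing centres it has 16 − 2 = 14 degrees of freedom and a critical value of 2.145 instead of 1.96, a ratio of 1.094. Combined with √DE at ICC 0.01, the interval is 1.067 × 1.094 = 1.17 to 1.091 × 1.094 = 1.19 times the uncorrected width. Power at ICC 0.01, assuming 50% against 70% improving and 14.8 patients in each of 8 centres per arm, is about 80%, which is the stated target.

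**The case against.** The strongest reply is that item 3 stands under a sentence that commits the tests and intervals to account for clustering. On that reading, item 3 means a chi-squared test corrected for the design effect, which is a standard method and performs well in step 4. The article never calls the test unadjusted. Naming the correction is the kind of detail a condensed article leaves to a full protocol or analysis plan, and neither is shown.

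Much of this stands. A reader might infer that the reported p-value will be too small and the interval too narrow. The document does not support that as a flat statement, because its opening paragraph promises the opposite. Had the article kept the general promise and named no test, there would be nothing to raise. But it names a test that does not deliver the promise unless modified, names no modification, and links random effects only to covariates. That is a conflict within one section and more than an omission.

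Two further points for the other side are fair. At ICC 0.01 the inflation is modest, and the larger figures rest on a value that the article does not give. Also, the 103 per arm can be reproduced with a continuity correction (assuming 30% against 50%, or 50% against 70%). If the test used that correction too, simulated error at ICC 0.01 would be 4.7 to 5.7% even with clustering ignored. The article says nothing about such a correction, and it would not protect at a higher ICC.

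A reader might also infer, from the heading that labels family physician variables as cluster level, that the random effect would sit on the physician and miss the centre. The article does not say so. It defines the cluster as the centre under both Design of the study and Unit of allocation, and a heading over a list of variables does not specify a model term.

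**Conclusion.** The point holds as an internal conflict. The section promises cluster-adjusted tests and intervals, names a test for the primary outcome that is not cluster-adjusted in its usual form, and does not say which of two analyses decides.

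The numerical consequence is conditional on item 3 being applied literally. It then amounts to a type I error of about 6.6 to 7.2% and an interval about 6 to 8% too narrow. This rests on the plan's ICC of 0.01, 14.8 to 20 patients per centre, and a two-sided test without continuity correction. Errors of 13 to 16% apply only under an assumed ICC of 0.05. I would rank this as worth correcting before analysis, with moderate confidence, and not as a demonstrated error in the trial's result.

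**What to change.** Rewrite item 3 so that it names one primary analysis accounting for the healthcare centre, the randomised unit. Two options are suitable:

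- a logistic model with a random intercept for centre and a small-sample correction for 16 clusters; or
- a t-test on the 16 centre proportions, with 14 degrees of freedom if all 16 centres contribute.

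These estimate different quantities (an odds ratio conditional on centre, and a difference in proportions), so one must be chosen before the data are seen. With either, report a cluster-adjusted 95% confidence interval for the difference in proportions. Drop the chi-squared test or label it descriptive, and describe any covariate-adjusted model as supportive unless it is the analysis chosen. Bring the abstract into line.

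The change is to wording only and needs no additional patients or data. The price is a slightly larger p-value and a somewhat wider interval than the uncorrected ones, as step 5 of the working shows.

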## Discussion

The proposed implementation strategy should have impact at four levels: increasing the knowledge of clinical physicians and patients; changing attitudes; changing the habits and behaviour of professionals in their clinical practice, while taking into account the patient's preferences, as well as administrative and economic influences; and modifying results, which means improving the quality of care and, finally, the health of the population by following CPG recommendations [37,38]. In this study, we will focus on checking the degree of suitability of the guideline recommendations (in terms of treatment, referral to mental health services, and information to the patient) in the clinical practice. We will also check if health outcomes (anxiety and quality of life) are improving.

If the intervention proposed is effective, it could be generalized to other common problems present in primary care. The findings of the study can also inform a future updates of the guideline. The 'Guiasalud' project includes a methodological manual for GPCs implementation [39]; the study outcomes may serve, moreover, to evaluate this manual.

In addition, our project seeks to enhance the importance of multidisciplinary teams working in the design, implantation and evaluation of CPGs.

As for the limitations of this study, the design selected for this project is the best possible given the intervention, while seeking to avoid possible contamination. Although the number of clusters is enough for the randomization to balance the potentially confounding factors among themselves, the following must be taken into account:

1. Given the nature of the study, the intervention cannot be masked.

2. There may be a classification bias, given the difficulty professionals have for making specific diagnoses, but this should be minimized by the information contained in the guideline.

3. Patients will be enrolled in the study by their own professionals. This increases variability in the approach, which will be minimized, on the one hand, by the training of all participating professionals and, on the other hand, by the protocolization of the research and the implementation of the computer application of the data collection log in the computer programme. Moreover, the fact that the professionals themselves enrol patients will increase applicability in regular practice.

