4. Although losses are contemplated in the follow-up, these are reduced in primary care because of the proximity of users to the system.

5. There may be a selection bias, because the selection and inclusion of patients will take place after randomisation of clusters. In order to be able to evaluate this bias, the information of those persons who decline to participate for each intervention group will be collected and compared.

In summary, the main contribution of our project is that it seeks to identify an effective strategy for implementing a CPG for the management of a common disorder present in primary care. Ensuring the appropriate uptake of guideline recommendations can reduce clinical variation and improve the care patients receive.

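### No covariate adjustment is named for the three guideline-compliance outcomes, although confounders are controlled for the primary outcome and recruitment after cluster randomisation may leave the arms different in case mix

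*Protocol article*

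**What the plan says.** In the Protocol article, Statistical analysis, item 4 gives one rule for all secondary response variables: their results "will be compared based on the group assigned by calculating the difference in proportions of each variable". It names no model and no covariates.

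Item 3 treats the primary outcome differently. The percentages improving by two or more Goldberg points are compared "in both groups by the chi-squared test, and the confidence interval of the difference will be calculated". Then: "Confounding variables will be controlled with multivariate analysis based on logistic regression with random effects". The Abstract also mentions adjustment for prognostic factors only after describing the main effectiveness analysis.

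The section's opening statement, "The use of the design by clusters chosen will be taken into account in all phases of data analysis", applies to item 4 as well. It concerns clustering, not confounding.

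The Discussion says, in limitation 5: "There may be a selection bias, because the selection and inclusion of patients will take place after randomisation of clusters". The response given there is that "the information of those persons who decline to participate for each intervention group will be collected and compared". Limitation 3 adds: "Patients will be enrolled in the study by their own professionals". Under Masking, patients, professionals and outcome assessors are all unblinded. Under Sequence generation, 16 centres are allocated by a simple random sequence.

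The clinical variables recorded are: "Previous episodes and treatment, diagnosis and current therapeutic plan, and reason for referral to mental health". Age and gender are also recorded, as are physicians' training in interview skills and in psychological techniques. Under Data collection method, the professionals' data are gathered before randomisation, apart from patient numbers (taken from the health information system) and opinions (collected at the end).

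**The concern.** Secondary objectives 1 to 3 are the direct test of whether the guideline was taken up, and the Discussion says the study will focus on them. Whether a patient is treated, informed or referred suitably can depend on that patient's history and on the professional's training.

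This design has a route by which those factors could differ between arms. Only intervention centres are trained, after allocation, in telling anxiety as a symptom from anxiety as a disorder. The same unblinded professionals then choose whom to enrol. With 16 centres and no stratification stated, chance imbalance between centres is also plausible.

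If such a difference arises, an unadjusted difference in proportions mixes it with the effect of the strategy. It could create an apparent gain or hide a real one. The primary and compliance results would also rest on different adjustment rules, and could disagree for that reason alone.

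**Working it through.** **1. The plan's own figure, used only to set precision.** Inputs from Sample size: alpha 0.05, power 80%, a 20% difference, 103 per arm before clustering, intracluster correlation 0.01, mean cluster size 20, loss 20%. The control rate is not stated. Two-sided, with continuity correction, 30% v 50% (or 50% v 70%) gives 103 per arm. Design effect = 1 + (20 − 1) × 0.01 = 1.19. Then 103 × 1.19 = 122.6, rounded up to 123, and 123 × 1.2 = 147.6, rounded up to 148. So 148 per arm and 296 in total are reproduced, with loss added as a multiplier. The present point does not depend on this figure.

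**2. Precision of a compliance comparison.** Expected completers per arm: 148 × 0.8 = 118.4. Effective number: 118.4 / 1.19 = 99.5. With compliance near 50% (assumed), SE = √(2 × 0.5 × 0.5 / 99.5) = 0.071.

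**3. Bias from one measured binary factor, with no true effect of the strategy.** Bias b = (difference in the factor's prevalence between arms) × (difference in compliance between patients with and without it). Two-sided false-positive rate = 1 − Φ(1.96 − b/SE) + Φ(−1.96 − b/SE). All imbalances and gaps are assumed, since the documents give none.

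| Prevalence imbalance | Compliance gap | Bias | False-positive rate |
|---|---|---|---|
| 10 points | 20 points | 2 points | 5.9% |
| 20 points | 20 points | 4 points | 8.7% |
| 20 points | 40 points | 8 points | 20% |
| 30 points | 40 points | 12 points | 40% |

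**4. Simulation with the clusters kept.** Assumptions: 8 v 8 centres; 15 analysed patients per centre (296 / 16 × 0.8 = 14.8); centre SD 0.25 on the logit scale; no true effect; a factor present in 40% of controls; 1,500 trials per scenario. The test is a centre-level t-test, so clustering is respected.

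| Imbalance | Odds ratio of factor for outcome | Bias without adjustment | False-positive rate |
|---|---|---|---|
| 10 points | 2 / 3 / 4 | 1.7 / 2.8 / 2.7 points | 4.1 / 6.1 / 6.6% |
| 20 points | 2 / 3 / 4 | 3.2 / 5.5 / 6.5 points | 7.9 / 10.9 / 14.7% |

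Removing the within-centre slope on the factor leaves at most 0.6 points of bias and rejection rates of 4.1-5.7%.

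**5. Agreement of the two checks.** Around 50% compliance, an odds ratio of 2 means about 58.6% v 41.4% (gap 17 points), and an odds ratio of 4 means 66.7% v 33.3% (gap 33 points). Step 3 then gives 1.7-3.3 points at a 10-point imbalance and 3.4-6.7 at 20, in line with step 4.

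**6. Scale.** The review cited in the Background (Strategies to implement CPGs) reports adherence gains of 6%, 7%, 8.1% and 14.1%. A bias of 2-3 points is well below these. A bias of 5.5-6.5 points is about as large as the smallest.

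**The case against.** The strongest reply is that item 4 is one sentence in a condensed article. It names an effect measure, does not say unadjusted, and a difference in proportions can itself be covariate-adjusted. Models and covariate lists for secondary outcomes are often left to a full protocol or analysis plan. This partly stands: a reader might infer that adjustment is excluded, and the text does not say so. But the article does state a rule for these outcomes, beside a fuller one for the primary outcome, so the difference between them is on the page.

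Two other stronger readings also fail. A reader might infer that the investigators expect selection bias and adjust the primary outcome for it. The Discussion says only that it may occur, its stated response is to compare decliners, and item 3 concerns confounders in general. A reader might also infer that the comparison ignores clustering, but the opening of the section covers that for every analysis.

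Some safeguards exist. Item 2 compares the groups at baseline, including prediction factors, and decliners are compared by arm. Both can reveal an imbalance, but neither corrects an estimate. Referral suitability is judged on guideline criteria, and treatment suitability presumably is too, so the outcome definitions may absorb part of the case mix. That would shrink the bias shown above by an unknown amount.

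The figures have limits. The imbalances and odds ratios are assumed. The simulated adjustment was a centre-level method, so it does not establish the error rate of a random-effects logistic model with 16 centres. Selection by unblinded professionals can also act on factors that nobody records.

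Finally, adjusting for everything recorded would be unwise. Diagnosis is made after randomisation by professionals whom the intervention trains in diagnosis, so allocation may affect it, and conditioning on it could introduce bias.

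**Conclusion.** The point holds in a conditional form. No covariate adjustment is named for the three compliance outcomes. The primary outcome has it, and the design gives a credible route to case-mix imbalance that the article itself acknowledges. Bias could follow. It is not shown that it will, because that needs both an imbalance in a factor and a link between that factor and compliance.

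The size is not fixed by the documents. With one measured factor and odds ratios of 2 to 4, it is about 2-3 points at an assumed 10-point imbalance, where the false-positive rate of 4-7% is close to nominal. At 20 points it is about 3-6.5 points, with a rate of 8-15%. Larger assumed gaps give more. This is a worthwhile and inexpensive improvement to the plan, not a flaw that invalidates the trial.

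**What to change.** In item 4, state that treatment suitability, information received and referral suitability, as binary outcomes, will be analysed with the random-effects logistic model of item 3, with a random effect for the primary healthcare centre. Item 3 names no covariates, so a short list must be prespecified: age, gender, previous episodes and treatment (dated before enrolment), and the professional's training as recorded before randomisation. These are characteristics that the strategy cannot change.

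Report the result also as an adjusted difference in proportions, beside the unadjusted difference with a cluster-adjusted confidence interval. Use diagnosis only in a sensitivity analysis.

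The cost is a sentence or two and a few more model fits, with no new data or patients. The drawbacks are an odds-ratio scale unless the result is converted, and no protection against unmeasured selection, for which the comparison of decliners remains necessary.

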### Secondary objectives

1. Evaluate the effectiveness of a CPG implementation strategy for the management of patients with anxiety disorders compared with the regular strategy, measured as the degree of suitability of the treatments (psychological, pharmacological, *et al*.) received by patients.

2. Evaluate the effectiveness of a CPG implementation strategy for the management of patients with anxiety disorders compared with the regular strategy, measured as the percentage of patients who have received the information proposed in the guideline (oral or written) about their disorder.

3. Evaluate the effectiveness of a CPG implementation strategy for the management of patients with anxiety disorders compared with the regular strategy, measured as the degree of suitability of referral to mental health services, based criteria established in the guideline.

4. Describe the professionals' opinion about the usefulness of the CPG.

5. Evaluate the effectiveness of a CPG implementation strategy for the management of patients with anxiety disorders compared with the regular strategy measured as a change in the patient's quality of life.

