### Patient variables (individual level)

#### Variables to measure health outcomes

1. Degree of anxiety, measured by the Goldberg anxiety subscale. The decrease in the score by two or more points compared with baseline score will be evaluated at six and twelve months.

2. Quality of life measured by means of the EuroQol 5D questionnaire. The quality of life will be evaluated at baseline, six months and twelve months.

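### The blanket difference in proportions for secondary outcomes does not fit EuroQol 5D: objective 5 asks for a change, and no rule is defined that would make it a proportion

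*Protocol article*

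**What the plan says.** Four places in the protocol article bear on this point.

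- **Statistical analysis, item 4.** The method for every secondary response variable is that results are "compared based on the group assigned by calculating the difference in proportions of each variable". No exception is made for quantitative variables.
- **Abstract, Method/design.** EuroQol 5D falls under that rule: "Secondary outcome variables include quality of life (EuroQol 5D), and degree of compliance with the CPG recommendations".
- **Secondary objectives, item 5.** The implementation strategy is compared with the regular one, "measured as a change in the patient's quality of life".
- **Variables to measure health outcomes, item 2.** The instrument and schedule are given: "Quality of life measured by means of the EuroQol 5D questionnaire", and "The quality of life will be evaluated at baseline, six months and twelve months". No threshold, category or particular score is named.

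Item 1 of that last section treats the Goldberg anxiety subscale differently and supplies a responder rule: "The decrease in the score by two or more points compared with baseline score will be evaluated at six and twelve months".

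**The concern.** Objective 5 is about a change in quality of life, and the schedule supports a within-patient comparison with baseline. A difference in proportions needs a yes/no outcome for each patient, and the protocol defines none for EuroQol 5D. An analyst who follows item 4 literally must invent a dichotomy; one who compares means departs from the stated method.

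Three things are at stake. Objective 5 has no defined estimate. Cutting a graded score in two discards information. A cut-point not fixed in advance can be chosen after the data have been seen. Quality of life is one of only two patient health outcomes in the protocol, and the Discussion says that the study will check whether it improves.

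**Working it through.** **1. Method against outcome.** The check is mainly one of reading.

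| Outcome | Form in the protocol | Yes/no rule given? | Fits a difference in proportions? |
|---|---|---|---|
| Goldberg anxiety (primary) | fall of at least two points from baseline | yes | yes |
| Information received (objective 2) | percentage of patients | yes, by its nature | yes |
| Suitability of treatment and of referral (objectives 1 and 3) | degree of suitability against the guideline | implied, if each patient is classed as suitable or not | yes, on that reading |
| EuroQol 5D (objective 5) | change, with measurements at 0, 6 and 12 months | no | not as written |

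**2. Does other text rescue it?** Item 2 of the Statistical analysis section matches tests to qualitative or quantitative variables, but only for the comparison of groups at the start of the trial. Item 1 is descriptive. Item 3 concerns the primary outcome. None of them supplies a method for EuroQol 5D.

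**3. Figures in the protocol.** The only calculation is the sample size for the primary outcome. It starts from 103 per arm. The design effect is 1 + (20 − 1) × 0.01 = 1.19, and 103 × 1.19 = 122.57. Adding 20% for losses gives 122.57 × 1.2 = 147.1, rounded up to 148 per arm, or 296. This reproduces the stated total but says nothing about EuroQol 5D, for which no figure can be recomputed.

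**4. Illustration of the cost of a cut-point.** These assumptions are not in the protocol: a normal score with standard deviation 1, a cut-off midway between the two arm means, two-sided alpha 0.05, and 103 effective patients per arm (the protocol's number before the design effect and losses).

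*Information kept.* Near the median, the proportion above the cut changes by φ(0) = 1/√(2π) per standard deviation of shift, and the binary variance is 1/4. Relative to the uncut score, the information is φ(0)² ÷ (1/4) = 2/π = 0.637. On that scale 103 patients act like 103 × 0.637 ≈ 66.

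*Power.* Let d be the standardised difference and p₂ = Φ(d/2), p₁ = Φ(−d/2) = 1 − p₂.

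- Means: Φ(d√(n/2) − 1.96).
- Proportions: Φ{[(p₂ − p₁)√n − 1.96√(2 × 0.5 × 0.5)] ÷ √(p₁(1 − p₁) + p₂(1 − p₂))}.

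For d = 0.4, the means formula gives 0.4 × √51.5 − 1.96 = 0.91, so the power is 82%. For proportions, p₁ = 0.421 and p₂ = 0.579, and the power is 63%.

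| d | Power, means | Power, proportions |
|---|---|---|
| 0.3 | 58% | 40% |
| 0.4 | 82% | 63% |
| 0.5 | 95% | 81% |

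With 148 × 0.8 ÷ 1.19 = 99.5 effective patients per arm instead of 103, the figures fall slightly: 56%, 81% and 94% for means, and 39%, 61% and 80% for proportions.

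**The case against.** **A dichotomy would be legitimate.** Objective 5 does not say mean change, and the protocol names no particular score. A prespecified responder rule or a set of categories would turn EuroQol 5D into a proportion. This stands: objective 5 is out of reach only under the text as written, not in principle.

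**Detail of this kind belongs in a fuller document.** An article may leave the definition of a secondary measure to the full protocol or analysis plan. But item 4 is not silent. It names a method and extends it to every secondary variable, and for one of them that method does not fit.

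**The numbers are generic.** No normal score, median split or effect size appears in the protocol, which plans tests for normality and does not assume it. This stands, and the figures are an illustration only.

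**Analysts are blinded to arm.** The Masking section says so. That lowers the risk of a favourable cut-point being chosen but does not supply the missing definition.

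Two stronger readings are tempting. A reader might infer that clustering is ignored for the secondary outcomes, because item 4 names no model while item 3 does. The opening of the Statistical analysis section applies the cluster design to all phases of the analysis, including confidence intervals and tests, so the protocol does not support that reading. A reader might also infer that using a proportion means ignoring baseline. The Goldberg responder outcome is itself a proportion built on change from baseline, so that does not follow either.

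**Conclusion.** The point holds in a limited form. The method in item 4 does not match objective 5 for EuroQol 5D, because no dichotomy is defined. The stated rule therefore yields no estimate of the change or leaves an open choice of cut-point. This rests on the text alone and needs no numerical assumption.

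The size of the loss cannot be derived from the protocol. Under the assumptions above, a median split keeps about 64% of the information, and power drops by about 14 to 19 percentage points for standardised differences of 0.3 to 0.5. An actual EuroQol 5D distribution or another cut-off would give other figures.

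The consequence is confined to one secondary outcome. The primary analysis, the sample size and the process outcomes are untouched. The wording should be corrected, but nothing in the design has to change.

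**What to change.** Reword item 4 in two parts.

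1. Restrict the difference in proportions to the binary process outcomes: suitability of treatment, information received and suitability of referral. The commitment at the head of the section to allow for the cluster design continues to apply to their confidence intervals and tests.
2. Name the EuroQol 5D score to be used. Analyse it at six and twelve months as a quantitative outcome, adjusted for baseline EuroQol 5D and with a random effect for the primary healthcare centre, for example in a linear mixed model. Report the adjusted mean difference between arms with its 95% confidence interval.

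If a EuroQol 5D responder proportion is wanted as well, define its threshold in advance and label it supplementary.

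The cost is a few sentences of analysis text. The baseline, six-month and twelve-month measurements are already planned, and neither recruitment nor the sample size changes.
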